Beyond the need for COAs that are responsive to change, there is also a need for complementary biomarkers including target engagement measures and measures of treatment response that can be used in early phase clinical trials. Specifically, magnetic resonance imaging (MRI) to measure intramuscular fat accumulations (IMFA) in the calf (Figure 1) (23, 24) has, in pilot studies, detected disease progression in CMT1A over 12 months, the most responsive assessment to date in this disorder. Sensory dysfunction contributes significantly to functional impairment and reduced quality of life in CMT1A, yet objective measures of sensory dysfunction are lacking in CMT1A, with sensory nerve action potentials often unelicitable. *In vivo* reflectance confocal microscopy is non-invasive, and painless and has detected reductions of Meissner corpuscle density (RCM of MC density) in CMT1A that correlate with elevations of touch pressure sensory thresholds and clinical severity (25, 26). These motor and sensory biomarkers require longitudinal, multicenter validation prior to application in CMT1A clinical trials.

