### MRI Assessment for Intramuscular Fat Accumulation

Initial pilot studies examined the utility of MRI to assess changes in muscle and identified fat fraction as a potential biomarker for studies in CMT1A. FF was found to correlate with the CMTES and demonstrated sensitivity to disease progression over a 12-month period (23). To validate this measure for multi-site use in future clinical trials, MRI muscle imaging of the lower extremities will be done using three-point Dixon MRI to assess the %FF of the bilateral thigh and calf muscles. Participants will be imaged feet-first supine with surface matrix coils for lower limb signal reception. Prior to participant enrolment, MRI studies of non-affected individuals will be performed and sent to a central site (UCL) for quality control and analysis (24). MRI scans for participants with CMT1A will also be sent to a central site for analysis.

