## Sample Size

We are recruiting 215 individuals with CMT1A to participate in this study. This baseline sample will provide >90% power to detect correlations between the CMT-FOM and existing COAs and PROs as small as 0.22. We anticipate that 180 participants will complete the assessments at the 30-month visit (accounting for up to a 15% dropout). This sample size will provide >80% power to detect significance of a mean change of 0.21 standard deviation units (effect size) using a paired t-test. This effect size was selected as one that is larger than those of existing adult scales such as the CMTNS (0.13) and the CMTES-R (0.20) (36, 37).

A sample of 60 individuals with CMT1A subjects at baseline will provide > 80% power to detect correlations between muscle FF and clinical outcome variables as small as 0.35, using a two-tailed test and a 5% significance level. Anticipating a dropout of 15%, a sample size of 51 CMT1A subjects at 24 months will provide 90% power to detect significance of a mean change of 0.46 standard deviation (SD) units (absolute increase in FF of 0.69%) (23) using a paired t-test. Sample sizes of 51 CMT1A subjects and 21 controls will provide 80% power to detect a group difference in mean change of 0.65%, assuming standard deviations of 1.5% in the CMT1A group and 0.4% in controls (23), using a two-sample t-test. Lastly, for validating RCM of MC density as a sensory biomarker a sample size of 135 CMT1A subjects at baseline will provide >90% power to detect correlations between MC density and clinical outcome variables as small as 0.28. Again, it is anticipated that 115 participants will complete assessments at 30 months which will provide 90% power to detect significance of a mean change of 0.31 standard deviation units using a paired t-test (36).

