Longitudinal analyses will be performed to evaluate responsiveness to change over time of MRI quantified muscle FF in the 60 adults with CMT1A. MRI scans will be evaluated at baseline, 12 and 24 months. Effect sizes and standardized response means will be computed for muscle FF. MMRM analyses will be performed to model mean changes over time in these outcomes (41). We will explore possible predictors of change over time using these models by adding interaction terms between covariates (e.g., age, sex, baseline severity) and month to the models. Mean changes over time, with corresponding 95% confidence intervals and *p*-values, will be obtained from these models. The results may suggest targeted eligibility criteria in future studies that will identify subjects more likely to change over time and, hence, increase power. Change in FF will be correlated with changes in the above clinical and electrophysiologic outcomes in CMT1A subjects to provide longitudinal validation of the MRI biomarker. This will assess whether early changes in FF are associated with longer term functional outcomes.

Reliability of MC density at digit V and the thenar eminence in participants with CMT1A will be assessed using a sample of 20 RCM image sets and two reviewers. Intra-rater reliability will be quantified using intraclass correlation coefficients (ICCs), estimated using a one-way random effects analysis of variance model with participant treated as a random effect. Interrater reliability will be evaluated using ICCs estimated using a two-way random effects analysis of variance model with participant and rater treated as random effects. The ICCs should exceed 0.80; any lower values will motivate us to reevaluate the scoring process and/or perform further training of the raters.

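### The 24-month fat-fraction power figures in absolute terms (0.69% and 0.65%) use SDs cited to a study described as 12 months long, with no stated rescaling, and are probably too favourable

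*Protocol article*

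**What the plan says.** The Sample Size section of the protocol article makes two statements about FF change.

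- One group: "a sample size of 51 CMT1A subjects at 24 months will provide 90% power to detect significance of a mean change of 0.46" SD units, glossed as "absolute increase in FF of 0.69%) (23) using a paired t-test".
- Against controls: "Sample sizes of 51 CMT1A subjects and 21 controls will provide 80% power to detect a group difference in mean change of 0.65" percent, "assuming standard deviations of 1.5% in the CMT1A group and 0.4% in controls (23), using a two-sample t-test".

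The 0.69% and both SDs carry the same citation. The section on MRI assessment says of that source that FF "demonstrated sensitivity to disease progression over a 12-month period (23"). The Introduction likewise says that FF has, "in pilot studies, detected disease progression in CMT1A over 12 months".

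The longitudinal MRI paragraph of Statistical Considerations schedules scans at baseline, 12 and 24 months. It plans covariate-by-month interactions whose results may help to "identify subjects more likely to change over time". The Discussion mentions a standardised response mean (SRM) above 0.8 for FF, with no follow-up period and no citation in that sentence.

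**The concern.** The follow-up period of the input does not appear to match that of the claim. The SDs come from work described as 12 months long, and the power is stated for 24 months. Nothing in the article says that the SD was rescaled or why it should stay the same.

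The SD of change from baseline is constant over follow-up only if it is all measurement error. If people progress at different rates, those differences accumulate and the SD grows. Two features of the article make some growth likely. The SD of change is 1.5% in CMT1A against 0.4% in controls, so if the control figure approximates scan noise, noise accounts for 0.16/2.25 = 7% of the CMT1A variance. The plan to look for faster-changing subgroups also treats differing rates as a real possibility.

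The absolute figures tell the reader what FF change, and what excess over controls, the MRI component can detect at its final scan. The Discussion presents the study as a basis for sample size and duration decisions in later trials, so the follow-up period to which an SD belongs matters here.

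**Working it through.** **Inputs (Sample Size section).** n = 51 CMT1A (60 × 0.85) and 21 controls at 24 months; 0.46 SD units; 0.69%; 0.65%; SDs 1.5% and 0.4%. Two-sided 5% is stated for the FF correlation and is assumed to apply to the t-tests.

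**Step 1. Reproduce the stated figures.**
- Implied SD: 0.69/0.46 = 1.5%, the same as the SD given for the control comparison.
- Paired: noncentrality 0.46 × √51 = 3.29 on 50 df gives 89.6% (stated 90%).
- Two-sample, unequal variances: SE = √(1.5²/51 + 0.4²/21) = √(0.0441 + 0.0076) = 0.2275; noncentrality 0.65/0.2275 = 2.86 on about 64 df gives 80.4% (stated 80%). A pooled-variance test would give only about 48%, so the unequal-variance form is used throughout.

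**Step 2. Let the SD grow (assumption).** Let w be the share of the 12-month variance that comes from stable person-specific slopes, the rest being error that does not accumulate. Slope variance is multiplied by 4 when follow-up doubles:

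SD(24) = 1.5 × √(1 − w + 4w) = 1.5 × √(1 + 3w).

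Hold the changes at 0.69% and 0.65% and the control SD at 0.4%. The paired noncentrality is 0.69 × √51 / SD(24); the two-sample noncentrality is 0.65 / √(SD(24)²/51 + 0.0076). For w = 0.10, SD(24) = 1.5 × √1.3 = 1.71, and these are 4.93/1.71 = 2.88 and 0.65/√(2.925/51 + 0.0076) = 2.55.

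| Slope share w | SD at 24 months | Power, 0.69% paired | Power, 0.65% vs controls |
|---|---|---|---|
| 0 (all error) | 1.50% | 90% | 80% |
| 10% | 1.71% | 81% | 71% |
| 25% | 1.98% | 68% | 59% |
| 50% | 2.37% | 53% | 46% |
| 100% (extreme) | 3.00% | 36% | 32% |

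**Step 3. Detectable change at 24 months.** At SD 1.5%: 0.69% (90%, paired) and 0.65% (80%, versus controls). At SD 2.12% (1.5 × √2): 0.98% and 0.88%. At SD 3.0%: 1.39% and 1.22%.

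**Step 4. Let the mean grow as well.** If the mean change doubles from 0.69% to 1.38% by 24 months, the standardised change is 0.92 divided by the SD ratio. At SD 2.12% it is 0.92/1.414 = 0.65 and paired power is above 99%. At SD 3.0% it is 0.92/2 = 0.46 and paired power is again 89.6%.

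**The case against.** **The calculation is correct.** Both powers reproduce, and the paired statement in SD units does not depend on the SD. This stands, so the problem is an unsupported input and not an arithmetic error. It does not protect the comparison with controls, which rests entirely on the absolute SDs.

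**The article never says that 1.5% is the SD of 12-month change.** The cited source and the full protocol are not at hand, and the figure may have been chosen or rescaled for 24 months. This stands as a caution. That it is an unscaled 12-month SD is a strong inference, because the only period the article attaches to that source is 12 months. If the SD was rescaled, one clause would settle the matter.

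**The size of any loss is not identified.** No slope variance is given. The search for predictors of change is exploratory and does not assert that rates differ. The scanner reproducibility work described used healthy or control subjects, so measurement error in fat-replaced muscle could exceed 0.4%. This also stands. A reader might take the control SD as the whole noise term and conclude that power must fall to about 64% and 56% or lower. The documents do not support that floor: the plausible range includes the stated 90% and 80%, and mild cases near them.

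**The mean change should grow too.** A reader might infer that the MRI component is underpowered. The documents do not show this. Step 4 keeps paired power at about 90% even if the SD doubles, provided the mean doubles. The SRM above 0.8 in the Discussion also exceeds 0.46, although it cannot be converted to a yearly rate because no period is given. Growth in the true mean does not, however, correct a statement about which absolute change is detectable at 24 months.

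**The study will estimate the 24-month SD itself.** True, but this does not justify the planning figure as printed.

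**Conclusion.** The point holds as an unstated and unsupported assumption: that the SD of FF change is the same at 24 months as in a source described as 12 months long. The absolute figures of 0.69% and 0.65% are probably too favourable for the visit to which they are attached. The 0.46 SD-unit figure and the arithmetic are sound.

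The size depends on an SD that the article does not give. Across slope shares from 0 to 100%, with the control SD held at 0.4%, power for the stated changes runs from 90% to 36% (paired) and from 80% to 32% (versus controls). Modest shares of 10% to 25% already cost about 9 to 22 points. The conclusion rests on two premises: that the 1.5% is a 12-month SD, which is inferred, and that at least some of it reflects lasting differences in rate, which is likely but not shown. It concerns the stated detectable changes only, not whether 60 recruited participants are enough.

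**What to change.** State in the Sample Size section the follow-up period over which the SDs of 1.5% and 0.4% were observed, and whether either was rescaled.

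If the period is 12 months:
- attach 0.69% and 0.65% to 12-month change, where at least 51 CMT1A participants should be available because 51 is the number expected to remain at 24 months;
- for 24 months, give the one-group figure in SD units only (0.46);
- for 24 months against controls, give a sensitivity range, for example a detectable difference of 0.65% to 1.22% at 80% power for CMT1A SDs of 1.5% to 3.0%, labelled as an assumption. If an absolute one-group figure is wanted, the matching range is 0.69% to 1.39% at 90% power.

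If the SDs were already set for 24 months, one clause saying so, with the basis, is enough.

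The cost is a sentence or two and less favourable stated figures. Recruitment, visits and analyses do not change.

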## Statistical Considerations

### Validation of the CMT-FOM

Preliminary studies of the CMT-FOM have documented feasibility, content validity, and concurrent validity (21). This study will further validate the CMT-FOM by assessing and documenting inter-rater reliability, performing Rasch analysis, and examining convergent validity and responsiveness. We will also determine the minimal clinically important change. We examined the inter-rater reliability of the CMT-FOM following the investigator meeting and the results have been reported (27). Using baseline data, we will document the internal consistency of the CMT-FOM with Cronbach's alpha.

Given that the CMT-FOM was based on the extensive validation of the CMTPedS (16), we hypothesize that it will be unidimensional and measure the construct of functional ability. We will examine the dimensionality of the CMT-FOM using principal component analysis and confirmatory factor analysis. Misfitting items will be examined and potentially modified, prioritizing integrity of outcome and concept validity. Rasch analysis will be performed on the CMT-FOM, including assessment of the response format, fit of the items, item bias, unidimensionality, and spread of items across the construct being measured (37).

Using data from the baseline visit, correlation and regression analyses will be performed to examine convergent validity. Specifically, we will examine the associations between the CMT-FOM and measures of disease severity (CMTNSv2-R, CMTES-R), patient reported outcomes, such as the CMT-HI, as well as electrophysiological outcomes. We anticipate finding correlations between the CMT-FOM and existing CMT1A measures, but not so strong as to make the CMT-FOM redundant.

To examine sensitivity to change, longitudinal analyses will evaluate the CMT-FOM in all affected subjects evaluated at 0 (baseline), 6, 12, 24, 30 and 36 months. The effect size and standardized response mean (SRM) are the most highly recommended measures of responsiveness (38). These two measures will be computed for CMT-FOM change from baseline, as well as changes in the CMTNSv2-R, CMTES-R, PROs (CMT-HI, PGIC), and the biomarkers at each time point (38, 39). The effect sizes and SRM will be compared between measures using bootstrap resampling (40). Mixed model repeated measures (MMRM) analyses will model mean changes over time in these outcomes (41).

The minimal clinically important change of the CMT-FOM will be estimated by anchor-based and distribution-based methods (42, 43). Anchor-based methods will use the PGIC questionnaire. Mean changes in the CMT-FOM will be calculated at 12 and 24 months for subjects in each of the five categories. Receiver operating characteristic (ROC) curve analyses will be performed separately for the 12- and 24-month outcomes to identify the change in CMT-FOM that best discriminates subjects who stated that their health got “a little” or “a lot” worse compared to those who did not. The 12, 24, 30 and 36-mo. changes in the CMT-FOM that correspond to effect sizes ranging from 0.30 to 0.50 standard deviation units will be described and compared to the minimal clinically important change.

For IMFA, muscle FF values for each subject will be combined into a summary measure for all muscles (left and right limb) at thigh and at calf level, and for relevant functional groups (quadriceps, hamstrings, anterior tibial compartment, and triceps surae) for left and right limbs separately (23). Using baseline data, cross sectional differences in muscle FF between the CMT1A group and matched controls will be assessed using analysis of covariance with group, age, and gender included in the model; large group differences are expected. Associations between FF and the COAs will be evaluated using correlation and regression analyses in CMT1A subjects.

Longitudinal analyses will be performed to evaluate responsiveness to change over time of MRI quantified muscle FF in the 60 adults with CMT1A. MRI scans will be evaluated at baseline, 12 and 24 months. Effect sizes and standardized response means will be computed for muscle FF. MMRM analyses will be performed to model mean changes over time in these outcomes (41). We will explore possible predictors of change over time using these models by adding interaction terms between covariates (e.g., age, sex, baseline severity) and month to the models. Mean changes over time, with corresponding 95% confidence intervals and *p*-values, will be obtained from these models. The results may suggest targeted eligibility criteria in future studies that will identify subjects more likely to change over time and, hence, increase power. Change in FF will be correlated with changes in the above clinical and electrophysiologic outcomes in CMT1A subjects to provide longitudinal validation of the MRI biomarker. This will assess whether early changes in FF are associated with longer term functional outcomes.

Reliability of MC density at digit V and the thenar eminence in participants with CMT1A will be assessed using a sample of 20 RCM image sets and two reviewers. Intra-rater reliability will be quantified using intraclass correlation coefficients (ICCs), estimated using a one-way random effects analysis of variance model with participant treated as a random effect. Interrater reliability will be evaluated using ICCs estimated using a two-way random effects analysis of variance model with participant and rater treated as random effects. The ICCs should exceed 0.80; any lower values will motivate us to reevaluate the scoring process and/or perform further training of the raters.

Baseline associations between MC densities and the touch sensation thresholds and FF of the calf muscle will be examined using correlation and regression analyses. Also at baseline, differences between CMT1A subjects and controls with respect to mean MC density will be evaluated using analysis of covariance models that include group as well as age, gender, hand dimension (if appropriate), and height. For longitudinal data, MMRM analyses will be performed to model mean changes over time in the MC density outcomes (41). We will explore possible predictors of change over time using these models by adding interaction terms between covariates (e.g., age, sex, baseline severity) and month to the models. Mean changes over time, with corresponding 95% confidence intervals and *p* values, will be obtained from these models. Changes in MC density will be correlated with changes in the COAs, touch sensation thresholds, ONLS and PROs in CMT1A subjects to provide longitudinal validation of this sensory biomarker.

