## Measures

To address the objectives of this study, participants complete assessments at baseline, and every 6 months for up to 36 months. Depending on the time of enrollment, participants will complete either a 30- or a 36-month end of study visit, but not both. Participants will be asked to complete the CMT-FOM, MRI and RCM assessments (Table 1). In addition, measures of disease severity and burden, sensory assessments, the fibular distal compound muscle action potential (CMAP) recording from the tibialis anterior muscle, and blood specimens will be collected. Participants will also complete a global impression of change questionnaire.

**Table 1 T1:** Schedule of activities.

**Study visit**		**Screen**	**1**	**2**	**3**	**4**	**5**	**6**
Timeframe (months)		0	0	6	12	24	30	36
Activities for all participants	Informed Consent	x						
	Demographics	x						
	Medical history	x		x	x	x	x	x
	Concomitant medications	x		x	x	x	x	x
	CMTES	x	x	x	x	x	x	x
	CMTNSv2-R (CMTES + tadial SNAP and ulnar CMAP)*		x		x	x		x
	Peroneal [tibialis anterior (TA)] CMAP amplitude		x		x	x		x
	CMT-FOM (up to 10 subjects will also perform CMT-FOM reliability testing)		x	x	x	x	x	x
	PROs: CMTHI, ONLS, PGIC		x	x	x	x	x	x
	Adverse Events	x	x	x	x	x	x	x
	Blood draw for Biomarkers		x	x	x	x	x	x
Additional AIM 2 items	MRI thigh and calf muscle IMFA		x		x	x		
Additional AIM 3 items	RCM MC density digit V and thenar eminence		x	x	x	x	x	x
	Monofilament touch sensation threshold testing		x	x	x	x	x	x

*SNAP, sensory nerve action potential; CMAP, compound muscle action potential*.

*^*^Nerve conduction studies will be conducted at 30 month visit when end of study for that subject*.

*Subjects will have either visit 5 (30 months) or visit 6 (36 months) depending on when they enroll. They will not have both. Subjects will be informed at time of enrollment whether they will have a 30 or 36 month visit*.

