### Additional Assessments

The CMTNS is a composite measure of disease severity that was developed for use in clinical trials (29). It includes items assessing sensory and motor symptoms, sensation (vibration and pinprick), distal limb strength and limited nerve conduction studies. Following the studies of ascorbic acid in CMT1A, (11, 12) it was modified to improve sensitivity and minimize floor and ceiling effects (CMTNSv2) (14). Most recently, Rasch analysis was applied resulting in the CMTNSv2-R (15). The CMT Exam score (CMTES-R) removes the ulnar motor (CMAP) and radial sensory action potentials (SNAP) amplitudes from the CMTNSv2-R and has been found to be more responsive than the CMTES (30).

Monofilament touch sensation threshold testing will be performed in all participants at the skin sites of *in vivo* RCM of MCs at the hand (digit V and the thenar eminence). Testing will be performed using a 2 Alternative Forced-Choice Stepping Algorithm (31) with a Logarithmic Filament Set. This filament set consists of a series of 9 monofilaments producing magnitudes of force of −3 to 5 in grams in natural log increments at 5/6 of their extended lengths. The nine levels of stimulus forces are available to define 19 threshold levels (32).

The Overall Neuropathy Limitation Scale (ONLS) is a clinician-administered assessment where participants are asked a series of questions about their symptoms and their ability to perform certain tasks and movements. This activity-level measure is designed to distinguish between limitations of upper and lower limbs in individuals with peripheral neuropathies (33).

The CMT Health Index (CMT-HI) is a patient-reported, disease-specific measure of disease burden that was developed for use in clinical trials involving adults with CMT (34). It has been shown to be reliable and valid and has been translated into Italian for multi-site clinical trial use (35).

The Patient Global Impression of Change (PGIC) questionnaire inquires about total health and health related to the symptomatic themes assessed in the CMT-FOM. Participants will be given the option to state that, compared to baseline, their health is: “1—a lot worse”; “2—a little worse”; “3—the same”; “4—a little better”; or “5—a lot better.” The PGIC will be used as an anchor to determine minimal clinically important change for the CMT-FOM.

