## Discussion

While CMT1A is the most common type of CMT, accounting for over 50 percent of cases, it is still a rare condition. CMT1A is slowly progressive; as such, it has proven challenging to measure disease progression with existing CMT outcome measures in the context of clinical trials. Multi-site studies are necessary to recruit sample sizes large enough to validate outcome measures and inform future clinical trial needs. The ACT-CMT study, has been designed to address these needs and prepare for future clinical trials in CMT1A. The eligibility criteria were selected to reflect the potential criteria for trials involving adults with CMT1A; however, the data from this study will likely be able to be leveraged to optimize eligibility criteria.

The CMT-FOM is hypothesized to be a unidimensional measure that with the CMTInfS and CMTPedS will provide whole of life CMT functional outcome measures. Initial studies have documented the reliability and supported the validity of this COA; however, this study will provide the sample size necessary for full validation, Rasch analysis, and examination of the ability of the CMT-FOM to detect disease progression over a time period that is feasible for the conduct of multi-center trials. The ACT-CMT protocol will also promote rigorous validation of existing COAs that have been used in prior trials in CMT (including the CMTES and the ONLS) for comparison with the CMT-FOM. Moreover, we have recently developed and reported cross-sectional validation of a disease specific patient reported outcome measure (CMT-HI) to capture patient reported disease burden in CMT (34). The ACT-CMT protocol will permit careful longitudinal validation of the responsiveness to change of the CMT-HI. Insight into clinically meaningful change in outcome measures for hereditary neuropathies is lacking. The current protocol will rigorously assess the clinically meaningful change of each COA.

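### The PGIC is itself a rating of change since baseline, so the planned effect size for its change has no valid denominator, and its SRM would not be comparable with those of the other measures

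*Protocol article*

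**What the plan says.** The responsiveness plan is under Statistical Considerations, Validation of the CMT-FOM. It chooses two statistics: "The effect size and standardized response mean (SRM) are the most highly recommended measures of responsiveness". It applies them first to the CMT-FOM, "These two measures will be computed for CMT-FOM change from baseline", and then to "changes in the CMTNSv2-R, CMTES-R, PROs (CMT-HI, PGIC), and the biomarkers at each time point". Two uses follow: "The effect sizes and SRM will be compared between measures using bootstrap resampling", and "Mixed model repeated measures (MMRM) analyses will model mean changes over time in these outcomes". The PGIC is named explicitly in the list that all of this refers to.

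Additional Assessments describes the PGIC item: "Participants will be given the option to state that, compared to baseline, their health is" one of five categories, from 1 (a lot worse) through 3 (the same) to 5 (a lot better). The same section makes the PGIC the anchor for the minimal clinically important change of the CMT-FOM. The anchor analysis uses the raw categories: mean CMT-FOM change in each of the five, and ROC curves for worse versus not worse.

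Table 1 (Measures) has one combined row, "PROs: CMTHI, ONLS, PGIC", marked at every visit from visit 1 (month 0) onward.

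The Discussion says the study will validate "existing COAs that have been used in prior trials in CMT (including the CMTES and the ONLS) for comparison with the CMT-FOM". The ONLS is not named in the responsiveness list.

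**The concern.** Effect size and SRM summarise the change in a state score that is measured at baseline and again later. The PGIC has no state score, because each response already expresses change since baseline. Asking for the change in the PGIC is asking for the change in a change. The effect size also needs a baseline SD, and at month 0 the PGIC question has nothing to refer to.

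The plan intends the comparison of responsiveness between measures to show how the CMT-FOM performs against existing assessments, and the Discussion says the data will inform the choice of outcomes for future trials. An entry without a valid denominator, or one built on a different quantity from the rest, should not be in that comparison. The PGIC is also the yardstick for the CMT-FOM's minimal important change, which makes it an odd competitor in the same ranking.

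A smaller issue is that the ONLS, which the Discussion names as a comparator, does not appear in the list where the comparison is specified.

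**Working it through.** **The plan's nearest figure.** No stated number is disputed. For context, Sample Size gives more than 80% power for a mean change of 0.21 SD with 180 completers and a paired t-test. Taking two-sided alpha of 0.05 (stated there for the MRI correlations, assumed here):

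- Normal approximation: 0.21 × √180 = 2.817; 2.817 − 1.960 = 0.857; power = Φ(0.857) = 0.804.
- Noncentral t: power = 0.800.

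The figure is reproduced, and nothing below alters it.

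**Effect size for the PGIC.** The standard definition is effect size = mean change ÷ SD at baseline. There are three possible readings of the baseline:

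1. No month-0 rating is taken. The denominator does not exist.
2. A month-0 rating is taken, as Table 1 marks, and everyone gives the only sensible answer, 3. The SD is 0 and the ratio is undefined.
3. A month-0 rating is taken and some answers differ from 3. The SD is then response noise on a question with no referent. The ratio can be calculated, but its size depends on that noise.

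None of these gives an interpretable effect size.

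**SRM for the PGIC.** The standard definition is SRM = mean change ÷ SD of change. If the rating itself is taken as the change, an SRM can be formed as mean(PGIC − 3) ÷ SD(PGIC). Three assumed distributions over categories 1 to 5 (not from the documents) show that it is computable:

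| Assumed % in categories 1/2/3/4/5 | Mean | SD | (Mean − 3) ÷ SD |
|---|---|---|---|
| 2/15/70/10/3 | 2.97 | 0.670 | −0.045 |
| 5/30/50/12/3 | 2.78 | 0.832 | −0.265 |
| 15/45/30/8/2 | 2.37 | 0.902 | −0.699 |

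This statistic exists, but it standardises a single retrospective five-point judgement. The SRMs of the CMT-FOM, CMTES-R and the other listed measures standardise the difference between two separate measurements. A bootstrap contrast between them would compare unlike quantities, and the plan does not say that recentring is intended.

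**MMRM.** The sentence on mean changes over time covers the same list, so the mismatch carries over. A model of change from a month-0 PGIC has the same missing or meaningless baseline.

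**ONLS, side by side.** The Discussion names it for comparison with the CMT-FOM. Statistical Considerations uses its change as a correlate of change in Meissner corpuscle density. Table 1 places it in the PRO row, while Additional Assessments describes it as clinician-administered. The responsiveness list spells out its PROs as the CMT-HI and PGIC only.

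**The case against.** The strongest reply is that this is loose drafting with little consequence. An unusable PGIC entry would be dropped at analysis. Every comparison among the CMT-FOM, CMTNSv2-R, CMTES-R, CMT-HI and biomarkers would stand, as would the anchor analysis, which uses raw PGIC categories and no PGIC effect size. That is correct and limits the size of the point. It does not remove it: the article states an analysis that does not fit the instrument it defines, which is different from leaving detail to another document.

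Several stronger readings are tempting but not supported:

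- A reader might infer that both statistics are undefined. Only the effect size is; the recentred SRM can be computed.
- A reader might infer that a month-0 PGIC will be subtracted from later ratings. The plan does not say so.
- A reader might want to show that a tiny baseline SD would push the PGIC far above the other measures. The documents give no month-0 PGIC distribution from which to calculate this. The other measures also have no narrow common range: Sample Size cites 0.13 for the CMTNS and 0.20 for the CMTES-R and uses detectable changes of 0.31 SD for Meissner corpuscle density and 0.46 SD for fat fraction. The Discussion cites a fat-fraction SRM above 0.8.
- A reader might take the month-0 mark as a deliberate PGIC assessment. It may only be a by-product of combining three instruments in one row, since the CMT-HI and ONLS do need that mark.
- A reader might conclude that the ONLS is excluded from the comparison. It may have been meant under PROs, as Table 1 groups it there, and the Discussion does not promise an effect size or SRM for it specifically.

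The view that an anchor should not also be ranked is partly a matter of judgement. Reporting the PGIC's own responsiveness would not contaminate the anchor analysis. The case for removal rests mainly on the missing baseline.

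**Conclusion.** The point holds in a limited form. The PGIC effect size lacks a valid denominator by the item's own wording. A PGIC SRM could be formed only as a different quantity that does not belong in the planned comparison. The passages that define the instrument and specify the analysis should be made to agree.

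The size is one entry in the responsiveness comparison, plus the corresponding MMRM. No power figure, CMT-FOM result, minimal-change estimate or comparison among the other measures changes. The conclusion assumes the usual definitions (effect size over baseline SD, SRM over SD of change), which the article names but does not write out. The ONLS omission is a genuine inconsistency but secondary, and may be unintended. The correction is worth making but is not critical to the study.

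**What to change.** 1. In Validation of the CMT-FOM, remove the PGIC from the list of measures given an effect size, SRM, bootstrap comparison and MMRM.
2. Keep the PGIC as the anchor for the CMT-FOM, and report its category frequencies at each post-baseline visit.
3. In Table 1, split the combined row or add a footnote so that the PGIC is not marked at month 0. The CMT-HI and ONLS keep their month-0 marks.
4. Name the ONLS in the responsiveness list so that it agrees with the Discussion.

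The cost is a few wording edits and one fewer questionnaire at visit 1. Any month-0 PGIC responses already collected can be left out of the analysis. The sample size does not change.
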